##### Secondary outcomes

A retrospective review of the electronic medical record will be used to clarify whether the patient has died during the observation period, and if so, for what reason.

The Modified Rankin Scale (mRS) is a clinician-reported measure of the patient’s degree of disability. It is widely applied for evaluating the outcome for stroke patients and as an endpoint in most randomized clinical trials [15]. It is a 7-level scale covering the entire range of functional outcomes from no symptoms to death. There is extensive evidence for the validity of the mRS, and the mRS categories correlate with the functional outcomes within the spectrum of stroke pathologies [16]. The limitations of the mRS are the subjective assignment of categories and the reproducibility of the score by examiners and patients [17]. A systematic review and meta-analysis of studies describing interobserver variability of the mRS reported pooled reliability (across 10 studies, *n* = 587 patients) of *κ* = 0.46 and a weighted *κ* of 0.90 [18]. To reduce interobserver variability, all members of the research group will be certified in the use of the mRS (http://rankinscale.org/).

The Short Form-36 Health Survey is a validated, 36-item, patient-reported measure of health-related quality of life (HRQOL) that has been used in a wide spectrum of medical conditions [19–21]. It is one of the most extensively used tools to measure health-related quality of life. It covers eight dimensions of HRQOL (physical functioning, role-physical, bodily pain, general health, vitality, social functioning, role-emotional, and mental health) and has an item on general health perception. Dimension scores can be summed together with differing weightings to generate two summary scores—a physical component score and a mental component score. Higher scores indicate higher HRQOL, and the SF-36 scores range from 0 (worst) to 100 (best) [21]. In the DRAIN-TIME 2 study, the first SF-36 is completed during the initial hospital stay with assistance from a member of the research group. The questionnaire is completed electronically in the REDCap database, via a computer or tablet (Ipad). A second SF-36 questionnaire is given to the patient at discharge and is also sent by secure electronic post (E-boks) to the patient 85 days after surgery. A member of the research group will ring the patient and assist with the completion of this questionnaire after 3 months (approx. 90 days). The responses are entered directly into the online REDCap database.

Using the electronic medical record system, we will collect several data points of interest throughout the study period: number of hours post-surgery before the patient is mobilized and length of hospital stay (i.e., at the department of neurosurgery before discharge to home or transfer to another hospital).

The following will be assessed by direct daily observation during admission to the neurosurgical department: complications related to immobilization (deep venous thrombosis and/or pulmonary embolism, brain infarction) and drain-related complications such as bleeding from the skin, pain, general discomfort, and infection.

#### Plans to promote participant retention and complete follow-up {18b}

The time to follow-up is 90 days, which we believe is a sufficiently short follow-up period to minimize patient attrition and maximize the completeness of data collection. Most symptomatic recurrent CSDH cases related to the primary operation are expected to occur within this time frame [22]. The primary outcome data (CSDH recurrence at 90 days) will be obtained through the electronic medical record. To limit participant burden related to follow-up visits, we will contact each participant by phone after 90 days. Here, we will assist the patient in completing the SF-36 questionnaire (which they will have received via e-mail/E-boks) and determine the mRS category. If a member of the research team assesses that it is not possible to obtain a valid assessment over the telephone, the patient and their relatives are offered attendance at the outpatient clinic.

#### Data management {19}

All patients admitted to one of the neurosurgical departments with a CSDH will be registered in REDCap, which is a worldwide online system developed specifically for non-commercial clinical research. REDCap is administered by the Open Patient data Explorative Network (OPEN) at Odense University Hospital, Odense, Denmark. The data entered will be stored on secure servers in the Region of Southern Denmark. Data are entered via an encrypted connection, are anonymized, and fulfill the demands for data protection. All data entries and changes are logged in REDCap and meet the Good Clinical Practice (GCP) requirements for the use of the electronic case report form (eCRF) in medical trials. The members of the research team are responsible for all data entry. Baseline data obtained from the medical record are registered at admission. After patient consent, online randomization is performed in REDCap. The database is updated when the patient is discharged. At 3 months follow-up, an electronic copy of the SF-36 questionnaire is automatically distributed via E-boks, which is an online secure digital mailbox linked to the patient’s personal Danish registration number.

#### Confidentiality {27}

All study-related information will be stored securely at the study site. All participant information will be stored in locked filing cabinets in areas with limited access. All laboratory specimens, data collection, and administrative forms will be identified by a coded ID [*identification*] number to maintain participant confidentiality. All records that contain names or other personal identifiers, such as informed consent forms, will be stored separately from study records identified by a code number. The electronic database (REDCap) is secured with password-protected access. Forms, lists, and any other listings that link participant ID numbers to other identifying information will be stored in a separate, locked filing cabinet in an area with limited access. Access to the electronic database (REDCap) and to the locked cabinets in areas with limited access is reserved exclusively to members of the national steering committee, DACSUHS. Data processing and statistical work will be performed by exporting the data from REDCap to a secure server. Participant confidentiality will always be maintained.

#### Plans for collection, laboratory evaluation, and storage of biological specimens for genetic or molecular analysis in this trial/future use {33}

A sub-study at Odense University Hospital and Rigshospitalet will be carried out. The biological specimens from this sub-study will be collected and stored in a biobank.

#### Overall objectives and background

Regardless of the choice of surgical procedure, there is a risk of spontaneous recovery/recurrence of the hematoma. Patients who develop recurrence experience significantly greater morbidity and mortality than patients who are cured after the first operation. In recent years, there has been an increasing interest in the composition of the hematoma fluid and in the systemic response as it is likely that the causes of hematoma expansion and recurrence will be found here. Therefore, we will collect hematoma fluid and hematoma membrane during the operation and will collect fluid from the drainage bag when the drain is removed after 6, 12, or 24 h. Furthermore, a blood sample before and after the operation will be obtained for the investigation of systemic changes. The biological material will be used for the analysis of pro- and anti-inflammatory as well as vascular (blood vessel-associated) proteins and peptides. A study of specific neurons and glia (markers of brain impact) will also be performed.

We hope that the study results will shed light on some of the crucial cerebral and systemic processes behind hematoma expansion and whether elimination (leaching) of particular proteins and peptides during surgery influences recurrence risk and postoperative neurological status. Finally, we hope to identify markers that can predict the risk of recurrence.

##### Plasma—collection procedures (methods)

A blood sample will be routinely taken at the time of admission and again on the first postoperative day. At the same time, an additional 10 ml of blood will be collected and distributed in five Sarstedt tubes (2× serum, 1× EDTA-coated, 1× citrate-coated, and 1× buffy-coated). The blood samples will be handled at the respective Departments of Clinical Biochemistry and Pharmacology, where pipetting, freezing, and storage will take place.

##### Chronic subdural hematoma fluid—collection procedures (methods)

Hematoma fluid will be collected from the subdural cavity using a 10-ml syringe. In the operating room, the fluid will be distributed into one Nunc tube of 3.6 ml and two Sarstedt EDTA tubes of 2 ml.

Postoperatively, hematoma fluid from the drainage bag will be retrieved using a 10-ml syringe. Bedside, the fluid will be distributed into one Nunc tube of 3.6 ml and two Sarstedt EDTA tubes of 2 ml.

The material will be picked up by relevant staff and transferred to the respective Departments of Clinical Biochemistry and Pharmacology, where further handling, freezing, and storage will take place.

##### Chronic subdural hematoma membrane—collection procedures (methods)

The hematoma membrane from the subdural cavity will be removed/biopsied (if possible) using appropriate instruments and divided so that half the tissue is fixed in formalin (buffered formaldehyde solution 4%) and the other half is frozen without fixation (− 80°).

All above samples will be logged in, and aliquots will be bar-coded with a unique storage ID generated by the REDCap system. The scientists who carry out the analyses on these materials will not have access to the personal identifiers and will not be able to link the results of these tests to personal identifier information. No individual results will be presented in publications or other reports. Participants will not be informed on an individual basis of any results from these studies.

## Statistical methods

### Statistical methods for primary and secondary outcomes {20a}

#### Primary outcome

Recurrence will be treated as a binary outcome (instead of a time-to-event outcome) due to the time to recurrence being of minor clinical interest compared to the occurrence of the event itself which is of major clinical relevance. As an effect measure, we consider relative risks due to their natural interpretability.

We will use relative risk regression with treatment assignment (6 h vs. 12 h vs. 24 h drainage time) as a categorical covariate and take the different trial centers into account. Adjusted risk ratios with 95% confidence intervals for recurrence rate will be reported. We investigate a non-inferiority hypothesis with a non-inferiority margin of 7% (see the “Sample size {14}” section). We will make two comparisons—one for each experimental arm (6 and 12 h) versus the common control arm (24 h) using likelihood ratio tests. We will use a one-sided test together with stage-specific significance thresholds equaling 0.5, 0.3, 0.2, 0.1, and 0.025 for each of the five stages.

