##### Sample size calculations

The MAMS design required the choice of a number of stages together with the choice of stage-specific decreasing significance levels together with stage-specific power levels, which result in an overall power and a familywise error rate. To inform this decision, we calculated several different designs considering two up to five stages. Stage-specific design parameters were in a try-out manner picked such that the overall power and FWER were approximately equal to 0.8 and 0.028, respectively. Especially, stage-specific significance levels for the initial stage of 0.5, 0.3, and 0.2 were considered. The final design choice was obtained from balancing the resulting expected sample sizes (for different numbers of non-inferior treatment arms) with a greater weight on the sample size in absence of non-inferior treatment arms. This resulted in a final design with five stages and decreasing stage-specific significance levels of alpha = 0.5, 0.3, 0.2, 0.1, and 0.025 together with stage-specific power levels of 0.9 for the first three stages and 0.95 for the last two stages. Stage parameters were chosen such that the overall power for the final comparison of each experimental arm (6 h or 12 h drainage) to control (24 h drainage) is approximately equal to 0.8. The familywise error rate corresponding to the design is approximately 0.028.

Assuming a recurrence rate of 16.3% on the basis of previous DACSUHS studies in all treatment arms (both experimental and control), equal allocation to all treatment arms, and a non-inferiority margin of 7%, we obtained the following cumulative sample sizes.

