### Methods for additional analyses (e.g., subgroup analyses) {20b}

Patients with CSDH recurrence at 90 days will be considered separately. Descriptive tables of CT-based hematoma subtypes, frequency of comorbidities, medications, gender, and descriptive summaries of patient age will be created.

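### The primary recurrence model adjusts for centre only; a few prespecified admission covariates could add modest precision at the later stages and the final analysis

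*Protocol article*

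**What the plan says.** All references are to the protocol article.

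- **Primary model.** Statistical methods {20a}, Primary outcome, specifies relative risk regression with treatment "as a categorical covariate and take the different trial centers into account". It then says that "Adjusted risk ratios with 95% confidence intervals for recurrence rate will be reported". Centre is the only adjustment variable named. Testing is by likelihood ratio: "We will use a one-sided test together with stage-specific significance thresholds" of 0.5, 0.3, 0.2, 0.1 and 0.025. Trial design {8} applies the same outcome and margin at interim and final analyses.
- **Data at admission.** Data management {19} states: "Baseline data obtained from the medical record are registered at admission". Table 2 (Participant timeline {13}) schedules GCS and mRS at admission.
- **Age, gender, medication, co-morbidity.** Outcomes {12} and the section on additional analyses {20b} name these only for describing patients who recurred: "frequency of comorbidities, medications, gender, and descriptive summaries of patient age will be created".
- **Power.** Sample size calculations gives "stage-specific power levels of 0.9 for the first three stages and 0.95 for the last two stages". Overall power for each experimental arm against control "is approximately equal to 0.8. The familywise error rate corresponding to the design is approximately 0.028".

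**The concern.** Eligibility is broad: any admission GCS, and both competent and incapacitated patients. Some of the variation in recurrence may therefore be predictable at admission. If so, a model with treatment and centre alone leaves that variation in the error term and gives wider intervals than the same patients could supply.

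The five-stage design makes this relevant. Its final comparison alone has power of about 0.95, but overall pairwise power is only about 0.80, because a truly non-inferior arm can be dropped at any of four interim looks. The maximum size is 2172 patients. Precision gained from data already in the database would cost no patient and no procedure. As planned, the candidate variables are tabulated only among patients who recurred, which does nothing for the comparison between arms.

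**Working it through.** **Inputs from the document.** Recurrence p = 0.163 in all arms; margin m = 0.07; one-sided alpha 0.5, 0.3, 0.2, 0.1, 0.025; stage powers 0.9, 0.9, 0.9, 0.95, 0.95; cumulative n per arm 91, 182, 344, 477, 724.

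**Step 1: reproduce the design.** n per arm = (z(1−alpha) + z(power))² × 2p(1−p) / m², with 2p(1−p) = 2 × 0.163 × 0.837 = 0.2729.

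| Stage | Formula | Printed |
|---|---|---|
| 1 | 91.5 | 91 |
| 2 | 181.6 | 182 |
| 3 | 251.0 | 344 |
| 4 | 476.9 | 477 |
| 5 | 723.6 | 724 |

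The printed stage 3 size matches a stage power of 0.95 (344.3), not the stated 0.9. That is a separate matter. With the printed sizes, the five-stage normal calculation gives overall pairwise power of 0.802 to 0.803 and a familywise error of 0.028. Both agree with the document.

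**Step 2: what adjustment could buy.** Prognostic strength is not in the document, so it is assumed here. For a baseline score with a given AUC, d = √2 × z(AUC), b = p(1−p)d², R² = b/(1+b). Adjusted variance is roughly (1−R²) times unadjusted variance.

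Example, AUC 0.70: d = 1.414 × 0.524 = 0.742; b = 0.1364 × 0.550 = 0.0750; R² = 0.070. Equivalent final n = 724 × 0.930, about 674.

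| Assumed AUC | R² | Final n per arm for equal precision | Overall pairwise power |
|---|---|---|---|
| 0.55 | 0.004 | 721 | 0.804 |
| 0.60 | 0.017 | 712 | 0.807 |
| 0.65 | 0.039 | 696 | 0.814 |
| 0.70 | 0.070 | 674 | 0.825 |

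This table applies the same proportional gain at every stage, so it is an upper guide.

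**Step 3: does the gain exist at interim sizes?** Stage 1 has about 91 × 0.163 = 15 events per arm. The simulation used four centres, four admission covariates, logistic standardisation to a risk difference, and equal risks. The entries are variance ratios, centre-only over adjusted; above 1 favours adjustment. Two separate runs are shown.

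| Logit SD of score | 91 per arm | 182 per arm | 724 per arm |
|---|---|---|---|
| 0 (useless) | 0.97, 0.97 | 0.99, 0.98 | 1.00, 1.00 |
| 0.4 (AUC 0.61) | 0.98, 0.99 | 1.01, 1.01 | 1.03, 1.02 |
| 0.6 (AUC 0.66) | 1.00, 1.00 | 1.05, 1.02 | 1.03, 1.04 |
| 0.8 (AUC 0.71) | 1.06, 1.05 | 1.08, 1.08 | 1.08, 1.09 |

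With six covariates in a log-link risk-ratio model at 91 per arm, the ratio was 0.94 to 0.98, a small loss throughout.

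**Step 4: overall power with stage-specific gains.** Putting such ratios into the five-stage calculation gives about 0.80 if the covariates are useless (a loss of at most about half a point) and about 0.804 to 0.811 at moderate strength, depending on the run and on interpolation for stages 3 and 4. A constant 8% variance reduction, close to the strongest case, gives about 0.828.

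**Step 5: error rate.** At the margin, final-stage rejection was 2.2 to 2.8% adjusted against 2.0 to 2.8% unadjusted, so adjustment does not disturb the one-sided 0.025 level.

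**The case against.** The strongest reply is that nothing here is wrong. Centre adjustment matches randomisation done separately in each centre, the model is valid, and the stated power is met without covariates. A covariate list often sits in an analysis plan, which is not shown, and the wording does not expressly forbid further covariates. Most of this stands, and it is why the point is one of efficiency only. What remains is that the article states a concrete model with one adjustment variable, so adding prognostic covariates would change what is written.

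A reader might infer that every interim and final test forgoes precision at no cost. The documents do not support that. They give no figure for prognostic strength. At 91 per arm the simulations show nothing gained at weak to moderate strength, and about 3% variance lost if the covariates are useless. It is equally tempting to argue that adjustment helps most at the early looks, where chance imbalance is largest; with about 15 events per arm it helps least there.

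Two further cautions stand. Only GCS and mRS are explicitly scheduled at admission. That age and medication are recorded for every patient is a reasonable inference from the admission registration, not a statement in the text. Log-binomial models with several covariates may also fail to converge: a basic solver failed in 26 to 86% of simulated trials at 91 per arm. That is a warning rather than an estimate, and logistic standardisation avoids the problem.

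**Conclusion.** The point holds as a modest missed efficiency. The likely benefit is from nothing to about 2.5 points of overall pairwise power (about 0.80 to 0.83), and under one point at moderate strength once the early stages are treated realistically. It accrues from stage 2 onward and mainly at the later stages. The size rests on assumed AUC values from 0.5 to about 0.71 and on the covariates being available for nearly all patients.

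A reader might also infer that adjustment cures the mismatch between a margin derived as a risk difference and a test specified on risk ratios. It does not: that is a separate issue. Standardised risks only make it possible to read the adjusted comparison on the scale on which the margin was derived.

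**What to change.** Before anyone sees results by arm, amend Statistical methods {20a}, Primary outcome, as follows.

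1. Name three or four covariates recorded before surgery, for example age, antithrombotic medication, admission GCS and admission mRS, and add them to centre in the primary model, at least from stage 2 and in the final analysis.
2. Estimate standardised (g-computation) recurrence risks per arm, so that the confidence limit of their difference can be set against the 7-point margin from Choice of non-inferiority margin.
3. Keep the centre-only model as a sensitivity analysis, and as the prespecified fallback at stage 1 or on non-convergence.
4. State a simple rule for missing baseline values.

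The costs are some programming, the missing-value rule, and a possible small variance loss at early stages if the covariates prove uninformative. The estimator and test also differ from the risk-ratio regression with likelihood ratio tests now specified, so this is more than adding a phrase. Sample size, alpha levels, margin and data collection stay as they are.

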#### Secondary outcomes

Mortality at 3 months will be analyzed by relative risk regression as with the primary outcome. SF-36, mRS, hours until mobilization, and length of hospital stay will be analyzed by linear or ordinal regression. The occurrence of different types of complications among the three study groups will be analyzed with a log-linear Poisson regression model.

For all secondary outcome measures, we investigate the superiority of each of the two experimental arms compared to the active control arm at the final analysis.

We use two-sided tests with a significance threshold of 0.05.

The data analysis will be an intention-to-treat analysis.

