**Methods:**

DRAIN-TIME 2 is a Danish multi-center, randomized controlled trial of postoperative drainage time including all four neurosurgical departments in Denmark. Both incapacitated and mentally competent patients are enrolled. Patients older than 18 years, free of other intracranial pathologies or history of previous brain surgery, are recruited at the time of admission or no later than 6 h after surgery. Each patient is randomized to either 6, 12, or 24 h of passive subdural drainage following single burr-hole evacuation of a CSDH. Mentally competent patients are asked to complete the SF-36 questionnaire. The primary endpoint is CSDH recurrence rate at 90 days. Secondary outcome measures include SF-36 at 90 days, length of hospital stay, drain-related complications, and complications related to immobilization and mortality.

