**Assessments**					
***Routine labs***	X		X		
***GCS***	X		X		
***mRS***	X		X		X
***Clinical examination***	X				
***SF-36***	X		X^#^		X
***Economic data***					X
***CSDH fluid****		X			
***CSDH membrane****		X			
***Blood****	X				

Schedule of assessments

*Ad* admission, *IO* intraoperative, *D* day, *mon* months, *GCS* Glasgow Coma Scale, *mRS* Modified Rankin Scale, *SF-36* Short Form (36) Health Survey

^*^Only collected in patients recruited to sub-study at Odense University Hospital and Rigshospitalet

^#^If not done the day of admission

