#### Assignment of interventions: allocation

##### Sequence generation {16a}

Participants will be randomly assigned to one of the three draining groups no later than 6 h postoperatively. Online randomization with a 1:1:1 allocation rate will be performed in each center using the REDCap randomize module in the REDCap database. Randomization is done separately in each center.

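### The stated models for SF-36, mRS, hours until mobilization and length of stay carry over neither centre nor the admission scores, which costs some precision

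*Protocol article*

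**What the plan says.** All references are to the protocol article.

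- **Statistical methods, Primary outcome.** The recurrence model uses treatment assignment "as a categorical covariate and take the different trial centers into account".
- **Statistical methods, Secondary outcomes.** The centre rule passes to one secondary outcome: "Mortality at 3 months will be analyzed by relative risk regression as with the primary outcome". The next sentence makes no such link: "SF-36, mRS, hours until mobilization, and length of hospital stay will be analyzed by linear or ordinal regression". It names no covariate. Each experimental arm is tested for superiority against 24 h, two-sided at 0.05.
- **Sequence generation {16a}.** "Randomization is done separately in each center". The abstract describes the trial as "including all four neurosurgical departments in Denmark".
- **Table 2.** mRS is scheduled at admission, day 1 and 3 months. SF-36 is scheduled at admission and 3 months, with a day 1 entry footnoted "If not done the day of admission".
- **Plans for assessment and collection of outcomes {18a}, Secondary outcomes.** "the first SF-36 is completed during the initial hospital stay with assistance from a member of the research group". Hours until mobilization and length of stay are taken from the medical record and arise only after surgery.

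**The concern.** Two kinds of information that the trial already holds have no stated use in these four models.

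The first is centre. Patients are randomized within it, and the same part of the article uses it for recurrence and mortality. If arms are balanced within centre, a model without centre leaves between-centre variation in the residual, so standard errors are somewhat too large.

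The second is the admission score for mRS and SF-36. An outcome measured on the same scale before and after treatment is normally analysed with the earlier value as a covariate, because this removes variation between patients that has nothing to do with the allocated drainage time.

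Faster mobilization and shorter stay are part of the trial's stated hypothesis (Trial rationale). Function and quality of life are not in that hypothesis, but the Discussion presents them as the way to judge the overall effect on patients. The article states no power for any of these outcomes, so precision that costs no extra patients is worth having.

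**Working it through.** **Setting the models side by side**

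| Outcome | Stated model | Centre named? | Admission value collected? | Admission value used? |
|---|---|---|---|---|
| Recurrence | relative risk regression | yes | not applicable | not applicable |
| 90-day mortality | as for recurrence | yes, by reference | not applicable | not applicable |
| SF-36 at 90 days | linear or ordinal | no | yes, or day 1 | not stated |
| mRS at 90 days | linear or ordinal | no | yes | not stated |
| Hours until mobilization | linear or ordinal | no | none can exist | not applicable |
| Length of stay | linear or ordinal | no | none can exist | not applicable |

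**The plan's own figure.** The only sample sizes given are for recurrence. At the final stage, with 16.3% in both arms, margin 7%, one-sided alpha 0.025 and stage power 0.95:

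n = (1.960 + 1.645)² × 2 × 0.163 × 0.837 / 0.07² ≈ 724 per arm.

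This matches the stated 724, which is used below as the number per arm if no arm is dropped.

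**Unadjusted reference.** At 724 per arm, two-sided 0.05 and 80% power, the detectable difference is

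√(2/724) × (1.960 + 0.842) = 0.147 SD.

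**Adding the admission score.** With correlation r between admission and 90-day values, the residual variance is (1 − r²) times the unadjusted variance. The interval narrows by 1 − √(1 − r²), and the equivalent gain in patients is 1/(1 − r²) − 1. The values of r are assumptions.

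| r (assumed) | Variance removed | Interval narrower by | Power at 0.147 SD | Equivalent extra patients |
|---|---|---|---|---|
| 0 | 0% | 0% | 80.0% | 0% |
| 0.2 | 4% | 2.0% | 81.6% | 1/0.96 − 1 = 4% |
| 0.3 | 9% | 4.6% | 83.6% | 1/0.91 − 1 = 10% |
| 0.5 | 25% | 13.4% | 89.9% | 1/0.75 − 1 = 33% |

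Two limits apply.

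- The formula belongs to linear models. It fits SF-36 directly and ordinal mRS only approximately; in an ordinal model the gain shows mainly as power, because the adjusted odds ratio is a different (conditional) quantity.
- It holds for patients with a usable baseline. If only a fraction f has one, the variance removed is roughly f × r². For example, f = 0.5 (assumed) and r = 0.5 give 0.5 × 0.25 = 12.5%.

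**Adding centre.** If centre accounts for a share ICC of the variance and arms are balanced within centre, the adjusted standard error is √(1 − ICC) times the unadjusted one. The true size of an unadjusted nominal 5% test is 2 × [1 − Φ(1.96/√(1 − ICC))]. The ICC values are assumptions.

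| ICC (assumed) | Variance removed | Power at 0.147 SD with centre | True size of the test without centre |
|---|---|---|---|
| 0.01 | 1% | 80.4% | 4.9% |
| 0.05 | 5% | 82.0% | 4.4% |
| 0.10 | 10% | 84.0% | 3.9% |

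Omitting centre therefore makes the test slightly conservative. It does not raise the false-positive rate.

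**Which SF-36 scores can serve as baseline.** Every patient has the drain in place until the envelope is opened at 6 h, and until then only the operating surgeon knows the allocation (Who will be blinded {17a}). A score completed before that moment cannot reflect a difference in drainage time. A day 1 score can, because the allocation is known by then and the drain may already be out. Whether a score was completed before the envelope was opened is itself settled before the arms diverge, so an indicator for a missing baseline is also a safe covariate.

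**The case against.** The strongest objection is that the point is read from silence. The sentence names a family of models, does not settle which family goes with which outcome, and excludes no covariate. Covariate lists for secondary outcomes are commonly left to a full protocol or statistical analysis plan, and the article mentions a statistical plan that is not shown. This stands to the extent that one may not infer that the trial has decided against adjustment; no sentence says so. It does not dispose of the point. The section does not leave adjustment wholly to another document: it sets a centre rule for recurrence, extends it to mortality, and then gives a bare model for four outcomes from the same randomization.

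Further objections also limit the point:

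- A reader might infer that all four outcomes lack a baseline adjustment they could have had. Two of them arise only after surgery and have none.
- A reader might infer that length of stay varies strongly with local transfer practice, so that omitting centre is costly. The article only defines stay as ending at discharge or transfer. It says nothing on differences between centres, and the likely gain is small.
- SF-36 baselines will be incomplete. Some are first taken on day 1, and patients incapacitated at admission may have none. The gain for SF-36 is therefore smaller than the table's full-baseline figures.

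**Conclusion.** The point holds as a modest, nearly free improvement to the secondary analyses. Followed as written, the four models ignore the randomization stratum, and two of them also ignore a collected admission score.

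The loss is precision only. A reader might infer a biased or invalid comparison, but randomization protects the unadjusted estimates, and leaving out centre makes the tests slightly conservative if anything. The recurrence analysis, its margin and its sample size are unaffected.

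The size cannot be derived from the article, which gives no SD, correlation or ICC for these outcomes. Under the assumed ranges, baseline adjustment removes about 4% to 25% of residual variance where a usable baseline exists (r from 0.2 to 0.5), and centre about 1% to 10% (ICC from 0.01 to 0.10). The centre figures also assume that arms are balanced within centre.

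**What to change.** State the following for the final analysis, in the statistical analysis plan if not in the protocol:

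1. Include centre in the models for SF-36, mRS, hours until mobilization and length of stay, as is done for recurrence and mortality.
2. Adjust 90-day mRS for admission mRS. The day 1 value should not be used as baseline.
3. Adjust each 90-day SF-36 score for the corresponding first score if it was completed before the 6 h envelope was opened. Otherwise treat the baseline as missing, set it to a constant and add a missing-baseline indicator.
4. For hours until mobilization and length of stay, centre is the only one of these adjustments that applies.

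The cost is analysis wording; no new data or patients are needed. The small downside is handling late or missing SF-36 baselines. That requires the completion time relative to the opening of the envelope. The first SF-36 is entered in REDCap, where entries are logged, and the opening time is written in the medical record, so this should be recoverable. Secondary outcomes are reserved for the final analysis (Interim analyses {21b}), so the choice can be fixed before any of these comparisons is seen.
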